## Abstract

**Background:**

Range of motion deficits of the lower extremity occur in about the half of the children with spastic cerebral palsy (CP). Over time, these impairments can cause joint deformities and deviations in the children's gait pattern, leading to limitations in moblity. Preventing a loss of range of motion is important in order to reduce secondary activity limitations and joint deformities. Sustained muscle stretch, imposed by orthotic management in rest, might be an effective method of preventing a decrease in range of motion. However, no controlled study has been performed.

**Methods:**

A single blind randomised controlled trial will be performed in 66 children with spastic CP, divided over three groups with each 22 participants. Two groups will be treated for 1 year with orthoses to prevent a decrease in range of motion in the ankle (either with static or dynamic knee-ankle-foot-orthoses) and a third group will be included as a control group and will receive usual care (physical therapy, manual stretching). Measurements will be performed at baseline and at 3, 6, 9 and 12 months after treatment allocation. The primary outcome measure will be ankle dorsiflexion at full knee extension, measured with a custom designed hand held dynamometer. Secondary outcome measures will be i) ankle and knee flexion during gait and ii) gross motor function. Furthermore, to gain more insight in the working mechanism of the orthotic management in rest, morphological parameters like achilles tendon length, muscle belly length, muscle fascicle length, muscle physiological cross sectional area length and fascicle pennation angle will be measured in a subgroup of 18 participants using a 3D imaging technique.

**Discussion:**

This randomised controlled trial will provide more insight into the efficacy of orthotic management in rest and the working mechanisms behind this treatment. The results of this study could lead to improved treatments.

**Trial Registration Number:**

Nederlands Trial Register NTR2091

## Background

### Cerebral palsy

*"Cerebral palsy (CP) describes a group of permanent disorders of the development of movement and posture, causing activity limitations that are attributed to non progressive disturbances that occurred in the developing fetal or infant brain. The motor disorders of cerebral palsy are often accompanied by disturbances of sensation, perception, cognition, communication, and behaviour, by epilepsy, and by secondary musculoskeletal problems" *[1]. Spastic CP is the most common form of CP (85%) [2]. Muscle spasticity is a clinical symptom characterized by a velocity dependent resistance to passive stretch or movement [3]. At present, in developed countries, about 2 live born children per 1000 have Cerebral Palsy [4,5].

Range of motion (ROM) deficits in one or more limb joints are present in many children with spastic cerebral palsy with about the half of the children having ROM deficits in the ankle, knee and hip [6]. In clinical practice, it is assumed that a reduced ROM in a joint is caused by a relative shortness of the muscle tendon complex compared to the length of the bone and/or by enhanced stiffness of the muscle tendon complex [7,8].

The *Gastrocnemius muscle *is often spastic in children with CP [9]. As the *Gastrocnemius muscle *has origin at the femur and his insertion at the calcaneus, this muscle is a major determinant of the ankle and knee ROM. The *Gastrocnemius muscle *was found to be shorter and stiffer in children with CP (having reduced ankle dorsiflexion) compared to typical developing children [10] and is expected to play a major role in the cause of limited ankle dorsiflexion ROM (measured at full knee extension). This ankle dorsiflexion ROM may lead to equinus deformities in the ankle [11]. Furthermore, a short and stiff *Gastrocnemius muscle *may lead to a gait pattern with increased ankle plantar flexion and increased knee flexion in midstance [12,13]. Compared to children with typical gait patterns, children with deviated gait patterns are impaired in mobility [9] and are metabolically less efficient and less resistant to fatigue during walking [14]. To prevent equinus contractures and less efficient gait patterns, it is important to treat and prevent impaired ankle dorsiflexion [9].

### Effectiveness of stretch

It is recommended not to use surgical interventions to improve gait (and thus not to treat impaired ankle dorsiflexion ROM by using surgical intervention) until gait is matured [9]. Based on joint immobilization studies of animals, it is well known that sustained muscle stretch stimulates an increase in muscle length by addition of sarcomeres in series [15-17]. In analogy with these results it is expected sustained muscle stretch as treatment of spastic calf muscles, will lengthen these muscles and in particular the gastrocnemius. However, a systematic review about the effectiveness of passive stretching shows that there is conflicting evidence on whether passive stretching can increase the ROM in a joint in children with CP [18]. Two types of stretching were investigated: 1) Manual stretching and 2) Sustained muscle stretch. Manual stretching was defined as *"holding the targeting joint to the available end ROM manually for a set amount of time, expressed as seconds, and then releasing it" *[18]. Sustained muscle stretch was defined as *"holding the targeting joint to the available end ROM by mechanical means such as standing tables or position equipment for an extended period, expressed as minutes up to 5-7 hours a day" *(a duration of 30 minutes stretching was the most commonly chosen in the analysed studies) [18]. In this review it was concluded that there appears to be only some indications that sustained muscle stretch is preferable to increase joint ROM in children with CP compared to manual stretching.

### Orthotic management in rest

Although sustained stretch is not an evidence based treatment, it is often applied by the use of night splints that are part of the general management of children with CP [9,19,20]. "Night splints" are used during night and/or during rest periods during the day. Therefore, we prefer to use the term "orthotic management in rest" instead of "night splinting". Regarding the muscle of interest in this study, the *Gastrocnemius muscle *of children with spastic CP, sustained stretch is applied by using knee-ankle-foot orthosis (KAFO). Static KAFOs (with ankle and knee angle fixed) as well as dynamic KAFOs (with ankle angle imposed by a spring allowing movement) are used. These orthoses hold the ankle joint at the maximal angle of dorsiflexion at full knee extension.

Using KAFOs in rest could be more effective compared to using KAFOs during active moments of the day. It might be presumed that a KAFO with fixed knee joints limits mobility, and therefore, will likely not be worn during active moments of the day. Other orthoses, like AFOs that are often used during active parts of the day, do not necessarily stretch the Gastrocnemius Muscle as the knee is allowed to flex. Knee flexion will occur during, for example, walking and sitting. To the best of our knowledge, Tardieu et al. [21] is the only study that evaluates the efficacy of orthotic management in rest in children with CP. It reports the effectiveness of orthotic treatment at night in two children, but these results are not confirmatory, due to the limited study design: 1) the number of treated subjects (2) was small, 2) there was no control group, and 3) the subject's ankle dorsiflexion was measured in knee flexion rather than extension which is more consistent with a measure of the *Soleus muscle *length instead of the *Gastrocnemius muscle*. Therefore, more research is needed to establish whether their conclusions were correct and whether the *Gastrocnemius muscle *will adapt in the same way to sustained stretch as the *Soleus muscle*. Despite the reported limited evidence in the literature, the efficacy of orthotic management in rest is probably considered as general knowledge. It is supposed that a KAFO prevents for reduced ankle dorsiflexion ROM when the KAFO is worn for 6 or more hours a day.

The major aim of this study is to obtain insight in the efficacy of orthotic management in rest to prevent a reduction in ankle dorsiflexion at full knee extension (clinical part of the study). Differences in the efficacy of static and dynamic KAFOs will be investigated and compared as well.

### Morphological properties

Recent literature shows that the morphological properties of muscles in children with CP differ from those in typically developing children [22-24]. For example, muscle belly length and muscle volume are smaller in children with CP compared to typically developing children [10,22,23]. A smaller fascicle length and smaller muscle thickness is found as well in children with CP [10,24]. Mostly, the *medial gastrocnemius muscle *was investigated. However, very little is known about the development of these morphological properties during growth both in typically developing children and children with CP [25], and the mechanisms underlying the decreasing ankle ROM during development in children with CP are unknown. Such insight is required to improve treatments for preventing reduced ankle ROM. Since the ROM of a joint is thought to be determined by the passive slack length (i.e. the smallest length at which any force is exerted) of the muscle tendon complex in relation to bone length and by the muscle tendon complex stiffness, improved knowledge of the changes in muscle morphology will likely provide insight into the etiology of reduced ROM. It is expected that the passive slack length of the muscle tendon complex will be affected by architectural variables, such as fascicle length (ℓ_(fasc)_), muscle belly length (ℓ_m_), physiological cross- sectional area (A_f_), angle between fascicle and aponeurosis (*γ_(fasc)_) *and tendon length (ℓ_t_) [26-29]. The muscle tendon complex stiffness is determined by the size and length of the muscle belly fibres and by the amount and arrangement of connective tissues (parallel elastic components) of the muscle tendon complex [30].

The KAFO treatments tested in this study are assumed to prevent the development of a reduced ankle dorsiflexion at full knee extension by increasing the slack length of the *Gastrocnemius muscle *muscle tendon complex and by reducing the muscle tendon complex stiffness. However, even if effective, the question remains whether the muscle tendon complex slack length increases due to muscle architectural changes like increased fascicle length or due to the amount and arrangement of connective tissues of the muscle tendon complex or both (see Figure 1 for an overview of the different architectural parameters that determine the length of the *medial Gastrocnemius muscle*.

**Figure 1 F1:**
[figure not shown]
**Schematic overview of the different architectural parameters that determine the length of the muscle tendon complex of the *medial Gastrocnemius muscle***. Symbols are explained in the text.

Therefore, the secondary aim of this study is to evaluate how changes in ankle dorsiflexion are related to morphological changes in the *medial Gastrocnemius muscle*.

### Hypotheses

#### Clinical part

We hypothesize that children with Cerebral Palsy (CP) who are treated with a knee-ankle-foot orthosis (KAFO) will show a smaller decline in (or even increase in) ankle range of motion (ROM) into dorsiflexion compared to children not being treated with a KAFO. In addition, we anticipate that children who are treated with a static KAFO will show less of a response (i.e. they will have a larger decline or a smaller increase in ankle ROM into dorsiflexion) when compared to children being treated with a dynamic KAFO.

We expect that for children with CP, treatment with either KAFO will have a less negative change in gait or even a positive change in gait pattern. A positive change refers to less ankle plantar flexion and less knee flexion in midstance, compared to no KAFO treatment. The effects are expected to be more positive in children being treated with the dynamic KAFO compared to the children being treated with the static KAFO.

The level of mobility (GMFM-score) of children who are treated with either KAFO is expected to show a smaller decline or increase compared to children who are not treated with a KAFO. As above, the effects are expected to be larger in children being treated with the dynamic KAFO rather than in children being treated with the static KAFO

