#### Sample size calculation

Expecting a 5 degree change in ankle ROM (assumed as clinically relevant), with a standard deviation of 4.5 degrees, a significance level (α) of 0.05 that is corrected for comparisons between three groups using a Bonferroni correction (α = 0.0167), and a power level of 80%, 13 children in each group will be sufficient. The calculation takes five repeated measurements with a correlation coefficient of ρ = 0.7 into account. In this study, 66 participants (22 in each group) will be recruited to allow drop outs.

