### Statistics

Statistical analysis will be performed according to an "intention to treat" principle. All relevant subject characteristics, such as age, body weight and length, gender, clinical diagnosis, will be described by their mean value and standard deviation, or percentages. Differences between groups at baseline will be tested using linear regression techniques or Chi-square statistics. The effect of the intervention will be analysed using a multi-level analysis, with the primary and secondary outcome measures as dependent variables and treatment group and time as independent variables. To test for any differences in the changes of variables between groups, a treatment*time interaction is included as independent variable. Analysis are adjusted for treatment site (Amsterdam, Arnhem or St Louis). Covariates will be: 1) KAFO wearing time, 2) lower leg growth, 3) use of an AFO by day, 4) stretching exercises and 5) level of spasticity. The α-value will be set at 0.05.

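### The sample size section uses plain Bonferroni (0.0167) for three group comparisons and the Statistics section uses 0.05 with no correction; one step-down rule in both would settle this and recover power.

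*Protocol article*

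**What the plan says.** - **Aim and hypotheses.** The Background states: "The major aim of this study is to obtain insight in the efficacy of orthotic management in rest". Under Hypotheses, Clinical part, the first statement is that "children with Cerebral Palsy (CP) who are treated with a knee-ankle-foot orthosis (KAFO) will show a smaller decline in" ankle dorsiflexion range than children without a KAFO. The second begins: "In addition, we anticipate that children who are treated with a static KAFO will show less of a response".
- **Sample size calculation.** The planning effect and spread are given as "Expecting a 5 degree change in ankle ROM (assumed as clinically relevant), with a standard deviation of 4.5 degrees". Alpha is described as "a significance level (α) of 0.05 that is corrected for comparisons between three groups using a Bonferroni correction (α = 0.0167"). With 80% power, five repeated measurements and a correlation of 0.7, the result is 13 children per group; 22 per group are recruited to allow for dropout.
- **Statistics.** The test is described thus: "To test for any differences in the changes of variables between groups, a treatment*time interaction is included as independent variable". On the level it says only "The α-value will be set at 0.05". It mentions no Bonferroni correction, no pairwise comparisons and no order of testing.

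**The concern.** The article gives two levels for what appears to be the same set of comparisons. The choice matters in both directions. If the Statistics section means that each pair is tested at 0.05, the family-wise error is well above the 5% that the sample size paragraph set out to protect. If the sample size paragraph governs, each KAFO must clear 0.0167 separately, even after another pairwise difference has been established. With only three groups that is stricter than error control needs, and it costs most when one KAFO works somewhat less well than the other, which is what the second hypothesis expects. A choice between the two rules made after the data are seen would be hard to defend.

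**Working it through.** **Inputs** (Sample size calculation): difference 5 degrees, SD 4.5, alpha 0.05/3 = 0.0167, power 80%, five measurements, correlation 0.7, 13 per group needed, 22 recruited. Sidedness is not stated. Two-sided is assumed because it reproduces the plan's figure (one-sided gives 11).

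**1. The plan's own figure.** Variance factor for the mean of five measurements: (1 + 4 × 0.7)/5 = 0.76.

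n = 2 × 4.5² × 0.76 × (2.394 + 0.842)² / 5² = 12.89, so 13 per group. This agrees with the article. The same formula at 0.05 gives 9.66, so 10 per group. The stated 13 therefore rests on the correction that the Statistics section does not mention.

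**2. Error if each pair is tested at 0.05.** Simulating three equal group means gives a 12.2% chance of at least one false pairwise finding.

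**3. Why a step-down is enough.** There are three pairwise null hypotheses among three means. If two of them hold, the third must hold as well. So once one is false, at most one of the other two can be true, and testing both remaining pairs at 0.05 risks at most one false rejection at 5%. If all three are true, a false finding must first pass the 0.0167 step. Simulated family-wise error runs from 4.4% (all means equal) to 5.0%. The first step is identical to Bonferroni, so everything that Bonferroni rejects is still rejected.

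**4. What it gains.** Standard error of one pairwise difference: 4.5 × √(2 × 0.76/13) = 1.54 degrees with 13 per group, and 4.5 × √(2 × 0.76/22) = 1.18 with 22. With 22 per group a pair must differ by 2.394 × 1.183 = 2.83 degrees at 0.0167, against 1.960 × 1.183 = 2.32 degrees at 0.05. Simulated power for both KAFOs to be significant against control:

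| True effects, static and dynamic | Per group | Plain Bonferroni | Step-down |
|---|---|---|---|
| 5 and 5 degrees | 13 | 69% | 82% |
| 5 and 5 degrees | 22 | 94% | 98% |
| 3 and 5 degrees (illustrative) | 13 | 31% | 47% |
| 3 and 5 degrees (illustrative) | 22 | 55% | 71% |

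**5. The pooled contrast (mean of both KAFOs minus control).** Its standard error is 4.5 × √(0.76 × (1/26 + 1/13)) = 1.33 degrees with 13 per group and 4.5 × √(0.76 × (1/44 + 1/22)) = 1.02 with 22. If both effects are 5 degrees, its power at 0.05 is 96% (13 per group) and 99.8% (22), against 80% and 97% for one Bonferroni pair. If static has no effect and dynamic has 5 degrees, the pooled difference is 2.5 degrees:

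- 13 per group: 2.5/1.333 = 1.88, and Φ(1.88 − 1.96) gives 47%.
- 22 per group: 2.5/1.024 = 2.44, and Φ(2.44 − 1.96) gives 68%.

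As a gate, the pooled test would cap power for dynamic versus control at these values, against 80% and 97% under plain Bonferroni.

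**The case against.** The strongest defence is that 0.0167 is only a planning input, and that this is a journal article whose analysis plan is not shown. The Statistics section could mean an overall group test at 0.05, followed by pairs at 0.05. With three groups that sequence also controls family-wise error, and with 13 per group its power for both KAFOs is 83% (5 and 5 degrees) or 48% (3 and 5), so the step-down would gain nothing over it. This stands as far as it goes, but the section does not spell out any follow-up tests. The article also does more than leave the matter open: it states two levels that differ. It is also true that the gain is small if all 22 per group are kept and both effects are 5 degrees.

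A reader might infer something stronger: that the main hypothesis has no test, and that the trial would report no effect if static and dynamic each beat control with p = 0.03, although the pooled p is 0.012. The documents do not support this, for four reasons.

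- The 0.0167 level appears only in the sample size paragraph, so the article does not commit the final analysis to it.
- With equal effects and one interaction term per KAFO arm (an assumption), the overall test in that example gives chi-square = 2.17² × 4/3 = 6.28 on 2 degrees of freedom, p = 0.043, which is significant at 0.05.
- The step-down would not rescue the example either, since 0.03 is above 0.0167.
- Pooling is one reading of the first hypothesis. The gait and mobility hypotheses speak of either KAFO, which fits a comparison of each type with control, and static is expected to do worse, so equal effects are not the plan's own expectation.

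**Conclusion.** The point holds as a mismatch between two sections, together with an avoidable loss of power. Under the sample size paragraph's rule, a true benefit of both KAFOs is missed more often than necessary: the step-down recovers 4 to 16 percentage points across the four cases in the table. Under an uncorrected pairwise reading of the Statistics section, family-wise error is about 12%. The loss is small at 22 per group with 5 degrees in both arms. It is larger after dropout or if one KAFO does less well. The step-down does not change the chance of at least one significant pair, because its first step is the Bonferroni step.

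The figures assume two-sided tests, a normal approximation with known variance, and the plan's SD and 0.76 variance factor. The 3-degree effect is illustrative and is not taken from the article. The 13-per-group case uses the number the article itself calls sufficient. The absence of a pooled contrast is not an error in itself, and whether to pool is a trade-off.

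**What to change.** State one rule in both sections for the primary outcome. Name the three pairwise comparisons (static versus control, dynamic versus control, static versus dynamic). Compare the smallest of the three p-values with 0.0167; if it is significant, compare each of the other two with 0.05; otherwise stop. In the Statistics section, say that 0.05 is the family-wise level for these three comparisons.

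Report the pooled KAFO-versus-control difference with its confidence interval as a supportive estimate for the first hypothesis. Do not make the pairwise tests conditional on it.

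The cost is wording only. The 13 per group and the recruitment of 66 stand, because the first step keeps the 0.0167 level on which they were calculated. Compared with plain Bonferroni nothing is lost, since no comparison that Bonferroni would declare significant is given up.

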#### Morphological part

In this study, it is hypothesized that the tendon length, muscle belly length and fascicle length increase and the muscle tendon complex stiffness decreases due to exposure of the *medial Gastrocnemius muscle *to sustained stretch.

## Methods

This study is approved by the Medical Ethics Committee of the VU University Medical Center and by the Institutional Review Board of the Washington University in Saint Louis.

### Participants

#### Criteria

The specific inclusion and exclusion criteria are shown in Table 1. Briefly, participants are children with spastic CP having been treated for reduced ankle dorsiflexion in the past, but not needed to be treated at the moment they were included into this study. Children are excluded from the study if they have a history of surgery of the *Gastrocnemius muscle *and/or *Soleus muscle *and/or selective dorsal rhizotomy, if they have severe enough morbidity or mobility limitations that prevent them from walking far enough to complete a gait analysis, or if they are being treated with intrathecal baclofen therapy (i.e. they have a current, active pump).

**Table 1 T1:** Inclusion and exclusion criteria

Inclusion criteria	Exclusion criteria
Children must have: 1. a clinical diagnosis of unilateral or bilateral spastic CP 2. an age between 4-12 years old 3. at least 0° ankle dorsiflexion with extended knee (physical examination) 4. a GMFCS class I, II or III 5. has been treated for reduced ankle dorsiflexion (< 5° dorsiflexion) before the start of the study by: a. and/or serial casting at least 3 months ago b. and/or botulinum toxin A injections in the *Gastrocnemius *and/or *Soleus muscle *at least 6 months ago c. orthotic management in rest with a knee-ankle-foot orthosis to prevent for decreasing ankle dorsiflexion 6. a stable social family situation	Children must not: 1. have had surgery of the *Gastrocnemius *and/or *Soleus muscle* 2. have had Selective Dorsal Rhizotomy 3. have had Intrathecal Baclofen therapy 4. have had Botulinum toxin A treatment in the lower extremity less than 6 months ago 5. have had casting of the lower extremity less than 3 months ago 6. have knee contractures (less than 0° knee extension) 7. have more than 20° ankle dorsiflexion at full knee extension 8. have behavioural problems (like severe mental retardation) 9. have significant sleeping problems 10. be institutionalised 11. be suffering from co-morbidity interfering with mobility that prevents them from walking adequate distance. 12. have problems with understanding either the Dutch (for subjects in the Netherlands) or English language

